### Sample size/power calculation

Sample size considerations in clinical studies start from what is considered a minimal clinically important difference. In studies of chronic low back pain, the ODI is commonly used as the main outcome measure, and a difference in 10 ODI points is considered clinically relevant [61,62]. This study, however, aims at investigating effect modification (by several candidate variables) of the treatment effect of surgical versus conservative treatment. This makes higher sample sizes necessary to have adequate power to answer the question [63,64].

We considered a series of scenarios for sample size calculations. To simplify the scenarios, we assumed a 1:1 distribution between patients undergoing surgical and conservative treatment, and a 1:1 distribution for the candidate effect modifier variable (e.g., gender).

We then made assumptions about the standard deviation of changes in ODI over a six-month period. From published studies and unpublished data sets we calculated scenarios with standard deviation ranging from 18 to 23 [14,16,21].

In general, an interaction effect of 0.4 to 0.6 of the main treatment effect is considered relevant.

These assumptions resulted in an array of sample sizes between 500 to 800 necessary to ensure 80% power to assess the hypothesized levels of effect modifications.

Furthermore, we assumed a 20% rate of patients who will not return on schedule to the six-month clinical visit at which the main outcome measurements will be conducted. These calculations showed that at least 800 patients should be included to provide 80% power to detect this interaction effect at a two-sided p of 0.05 [63]. However, as there is uncertainty about the distribution of effect modifiers, the proportion of patients opting for surgery, and the proportion that will not be seen at six months, we decided to set a target sample size of 1000 patients.

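### The stated 500 to 800 patients for 80% interaction power cannot be reproduced from the printed inputs

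*Protocol article*

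**What the plan says.** All the inputs stand in the Sample size/power calculation section of the protocol article. It opens with the principle that "Sample size considerations in clinical studies start from what is considered a minimal clinically important difference" and says that for the ODI "a difference in 10 ODI points is considered clinically relevant". It then explains that the aim is effect modification, which calls for larger numbers. The scenarios assume equal numbers treated surgically and conservatively and an evenly split modifier. On variability, "we calculated scenarios with standard deviation ranging from 18 to 23". On the target, "In general, an interaction effect of 0.4 to 0.6 of the main treatment effect is considered relevant". The result follows: "These assumptions resulted in an array of sample sizes between 500 to 800 necessary to ensure 80% power".

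Only after that result does the section bring in 20% non-return at six months. It then says that at least 800 patients should be included for "80% power to detect this interaction effect at a two-sided p of 0.05", and sets a target of 1000 to allow for uncertainty. The Feasibility of the study section expects 990 participants and, after 20% loss, 792 analysed.

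The section does not state the size of the main treatment effect to which 0.4 to 0.6 applies, how the interaction is defined, or whether 500 to 800 is counted before or after loss.

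**The concern.** An interaction that is about half of a main effect usually needs a far larger sample than the main effect does. The section names one ODI difference, 10 points. A reader will naturally take that as the main effect and the target interaction as 4 to 6 points. With SDs of 18 to 23, 500 to 800 then looks much too small.

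The printed range also looks too narrow for the two input ranges behind it.

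Effect modification is the question the sample size is built on, and the article's conclusions promise to identify patient groups who benefit from particular treatments. If the 80% figure does not hold for the interactions called relevant, readers will be misled about what the study can detect.

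**Working it through.** **Inputs** (Sample size/power calculation, except the last): two-sided 0.05; 80% power; 1:1 treatment; 1:1 modifier; SD of change 18 to 23; interaction 0.4 to 0.6 of the main effect; 10 ODI points as a clinically relevant difference; 20% loss; 792 analysed (Feasibility of the study).

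**Formula.** With four equal cells of N/4, the difference between subgroups in treatment effect has variance 4 × SD²/(N/4) = 16·SD²/N. So N = 16·(1.960 + 0.842)²·SD²/δ² ≈ 125.6·SD²/δ², where δ is the between-subgroup difference. Sample sizes are rounded to the nearest patient unless noted.

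**1. Trying to reproduce 500 to 800 with a main effect of 10** (δ = 4 to 6):

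| SD | δ = 4 | δ = 5 | δ = 6 |
|---|---|---|---|
| 18 | 2,543 | 1,628 | 1,130 |
| 23 | 4,152 | 2,657 | 1,845 |

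The range is 1,130 to 4,152 evaluable. A one-sided 0.05 test would give 891 to 3,271. Neither gives 500 to 800.

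**2. Plus/minus definition.** If the interaction is each subgroup's deviation from the average effect, the between-subgroup difference is twice as large, 8 to 12 points, and N falls fourfold: 1,130/4 ≈ 283 to 4,152/4 = 1,038. This interval contains 500 to 800 but does not match it, and its upper end exceeds 800.

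**3. A check that does not need the main effect.** N is proportional to (SD/ratio)². Across the full stated ranges the largest N divided by the smallest is (0.6/0.4)² × (23/18)² = 2.25 × 1.633 = 3.67. The printed range gives 800/500 = 1.6. Alpha, power, the interaction definition and a common loss allowance multiply every scenario by the same factor, so none of them changes this ratio. If the easiest scenario needs 500, the hardest needs 500 × 3.67 ≈ 1,840. If the hardest needs 800, the easiest needs 800/3.67 ≈ 218.

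**4. What does give roughly 500 to 800:**
- One fixed between-subgroup difference of 9 points gives 502 (SD 18) to 820 (SD 23). That is 0.6 of a main effect of 15. Extending the same main effect down to a ratio of 0.4 takes the top to about 1,845.
- One fixed difference of 10 points gives 407 to 665 evaluable (rounded up). Dividing by 0.8 gives 509 to 831; multiplying by 1.2 gives 489 to 798.
- A difference of 0.4 to 0.5 SD gives 785 to 502.

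The section describes none of these.

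**5. Power with 792 analysed.** The standard error is 4·SD/√792, which is 2.56 at SD 18 and 3.27 at SD 23. Power is Φ(δ/SE − 1.960):

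| Difference between subgroups | SD 18 | SD 23 |
|---|---|---|
| 4 points | 35% | 23% |
| 6 points | 65% | 45% |
| 8 points | 88% | 69% |
| 12 points | over 99% | 96% |

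The first two rows are 0.4 and 0.6 of a 10-point main effect read as a difference of differences. The last two are the same ratios read as plus/minus deviations.

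**6. Detectable difference.** At 80% power and N = 792, δ = SD × √(125.6/792) = 0.398·SD, which is 7.2 points (SD 18) to 9.2 points (SD 23).

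**7. Loss.** If 500 to 800 means evaluable patients, including 800 leaves 800 × 0.8 = 640, and the upper end needs 800/0.8 = 1,000 included. The target of 1000 would cover that; the stated minimum of 800 would not.

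**The case against.** The strongest objection is that 10 points is given only as a clinically relevant difference. The text turns from it to effect modification and never calls it the assumed main effect. The interaction definition is also unstated, and the cited method source is not available here. Under the plus/minus definition, with a main effect of 10 and the midpoint ratio of 0.5, the between-subgroup difference is 10 points. After a 20% allowance that gives 489 to 798 or 509 to 831, close to the printed range and to the figure of 800 included.

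Much of this stands. A reader might infer that the 80% claim is simply false and that true power is 23% to 65%. The article does not support that, because both statements rest on an assumed main effect and an assumed definition. Under the other definition power at 792 is 69% or better. Nor can it be said that no selection of scenarios gives 500 to 800, since step 4 of the working shows several. The 3.67-fold argument assumes one main effect crossed with the full ranges, whereas the text speaks of a series of scenarios. A reader might also infer that null interactions will be taken as proof of no modification. The article does not say so, and it calls for replication.

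The rescue still falls short. It uses one ratio where the text gives a range and claims power for the hypothesised levels generally. It also puts the 20% loss inside a range that is printed before loss is introduced.

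Covariate adjustment could reduce the residual SD, but the section claims no such gain. With a 10-point main effect and difference-of-differences coding, covariates would have to explain between 1 − 792/1,130 = 30% and 1 − 792/4,152 = 81% of the variance. A common reduction would leave the 3.67-fold spread unchanged.

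**Conclusion.** Wrong as written: the section says its assumptions yield 500 to 800 patients, and the assumptions it prints do not. This holds under either definition of the interaction. For any single main effect, the full stated ranges cannot produce a 1.6-fold spread.

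How large the shortfall is depends on what is left unstated. With a 10-point main effect and difference-of-differences coding, the need is about 1,130 to 4,150 evaluable patients and power at 792 is about 23% to 65%. With plus/minus coding the need is about 283 to 1,038, and only the harder scenarios fall short. All figures assume equal cells. The section itself is unsure of the modifier split and of the proportion choosing surgery, and imbalance would lower power.

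The loss step is a second, smaller ambiguity. It affects the stated minimum of 800, not the target of 1000.

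**What to change.** Keep the target of 1000. In the Sample size/power calculation section:

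- State the main treatment effect assumed, in ODI points.
- Define the interaction, either as the difference in treatment effect between subgroups or as the deviation of each from the average.
- Say whether 500 to 800 is before or after the 20% loss, and bring the minimum of 800 included into line with it.
- Replace the claim of 80% power for 0.4 to 0.6 of the treatment effect with what the design delivers: with about 792 analysed and balanced cells, 80% power for a between-subgroup difference in treatment effect of about 0.40 SD (7.2 points at SD 18 to 9.2 points at SD 23).
- If the 23% to 65% figure is quoted, label it as conditional on a 10-point main effect and difference-of-differences coding.

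The cost is rewording one section. No extra patients are needed and the design does not change. The downside is that the stated power becomes less favourable.

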The respective acquisition of patient data will be coordinated at the MEM Research Center and the University of Otago. 2200 patients will be assessed for eligibility in CH and NZ combined (see figure 1). It can be assumed that 75% of these screened patients will be found eligible for enrolment. Out of these 1650 patients, presumably 990 (60%) will agree to participate in this study. Up to 20% of the patients can be expected to be lost to follow-up in the worst case scenario, so that, finally, 792 patients will be analysed according to the intention-to-treat principle. This estimate is based on data provided by a recent prospective cohort study comparing surgical and conservative treatment in a LBP population, with ODI as primary outcome measures [21].

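### The minimum of 800 to include does not carry the 20% loss for scenarios needing more than 640 analysed, and in the top scenario the target of 1000 leaves no reserve

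*Protocol article*

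**What the plan says.** All but one of the statements are in the protocol article, Sample size/power calculation, in this order:

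1. Both the treatment groups and the candidate effect modifier are taken as split 1:1, to simplify. The standard deviation of ODI change is taken as 18 to 23, and "an interaction effect of 0.4 to 0.6 of the main treatment effect is considered relevant".
2. From these, between 500 and 800 patients are said to be "necessary to ensure 80% power to assess the hypothesized levels of effect modifications".
3. Loss is then introduced as a further assumption: "we assumed a 20% rate of patients who will not return on schedule to the six-month clinical visit".
4. The conclusion is that "at least 800 patients should be included to provide 80% power to detect this interaction effect", at a two-sided 5% level.
5. Because the modifier distribution, the share choosing surgery and the loss are uncertain, "we decided to set a target sample size of 1000 patients".

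The section Feasibility of the study expects 990 to enrol and up to 20% to be lost in the worst case, "so that, finally, 792 patients will be analysed according to the intention-to-treat principle".

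**The concern.** The number 800 appears twice in different roles. It is the upper end of the requirement before loss is mentioned, and it is the minimum to include after loss is mentioned. A 20% loss cannot leave the number unchanged if both figures refer to the same scenario.

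Two statements depend on this. The first is the claim of 80% power with 800 included. The second is the reason for going to 1000. If that step is used up by the 20% loss already assumed, it cannot also absorb the three uncertainties named as its purpose.

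This matters because effect modification is what drives the sample size. The Statistical Analysis section gives highest priority among co-interventions to cognitive behavioural therapy and return-to-work programmes. The cohort is observational, and nothing in it ensures a 1:1 split for surgery or for those co-interventions.

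**Working it through.** **Inputs from the protocol.** Requirement 500 to 800; loss 20%; minimum included 800; target 1000; planned 990 enrolled and 792 analysed; power 80%; two-sided 5%; both splits 1:1.

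**Can the stated 800 be reproduced?** Number to include = number needed / (1 − 0.20).

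- 500 / 0.8 = 625
- 640 / 0.8 = 800
- 800 / 0.8 = 1000

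The stated 800 follows only from a requirement of 640, a figure the protocol does not give. It does not follow from the upper end of the range. Conversely, 800 × 0.8 = 640 analysed and 1000 × 0.8 = 800 analysed. The feasibility chain is consistent in itself: 2200 × 0.75 × 0.60 = 990, and 990 × 0.8 = 792.

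**Power at the number actually analysed.** If N0 patients give 80% power, then N patients give Φ(√(N/N0) × (1.960 + 0.842) − 1.960). For example, with N = 640 and N0 = 800: Φ(2.802 × √0.8 − 1.960) = 70.7%.

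| Needed at 1:1 | 640 analysed (800 included) | 792 analysed (990 enrolled) | 800 analysed (1000 included) |
|---|---|---|---|
| 500 | 88.7% | 94.1% | 94.3% |
| 600 | 82.5% | 89.6% | 89.9% |
| 640 | 80.0% | 87.6% | 87.9% |
| 700 | 76.4% | 84.6% | 85.0% |
| 800 | 70.7% | 79.6% | 80.0% |

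**What the target leaves for unequal splits.** With surgical share p and modifier prevalence q, taken as independent, the requirement is multiplied by 0.0625 / [p(1−p)q(1−q)]. The protocol gives no expected splits, so those below are illustrative assumptions.

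| Split | Factor | Need if 800 at 1:1 | Power at 800 analysed | Need if 640 at 1:1 | Power at 800 analysed |
|---|---|---|---|---|---|
| 60:40 on one factor | 1.042 | 834 | 78.4% | 667 | 86.6% |
| 60:40 on both | 1.085 | 869 | 76.7% | 695 | 85.2% |
| 70:30 on one factor | 1.190 | 953 | 72.8% | 762 | 81.9% |
| 70:30 on both | 1.417 | 1134 | 65.3% | 908 | 74.9% |

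**Higher loss.** With 25% lost from 1000, 750 are analysed. Power is 77.4% if 800 are needed and 85.8% if 640 are needed.

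**Lower loss.** With an illustrative 10% lost, 900 are analysed. That exceeds the 869 needed for 60:40 on both factors, even in the top scenario.

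**The case against.** The best defence is that the protocol does not say whether 500 to 800 is before or after loss, or which scenario the 800 serves. The value 640 lies inside the range and 640 / 0.8 is exactly 800, so the loss may have been applied correctly to a mid-range scenario. The range may also already include loss. On either account the move to 1000 adds a real reserve: with 640 needed, 1000 included leaves 160 more analysed than required at 20% loss. The feasibility section also calls 20% the worst case.

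This stands as a limit on the point but does not remove it. Neither alternative is stated, and the order of the text favours the plain reading: the range comes from assumptions that do not include loss, and loss is then added. If 640 was the design scenario, the requirements between 640 and 800 are not met with 800 included, and the power claim should be limited accordingly.

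Three stronger readings are tempting but not supported:

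- A reader might infer that 80% power simply fails with 800 included. It fails only for scenarios needing more than 640.
- A reader might infer that 1000 holds no reserve at all, or that power fails as soon as either split leaves 1:1. That is true only for the scenario needing 800 at 20% loss.
- A reader might infer that the priority co-interventions will, by design, not reach half the cohort. The protocol gives no uptake figures and design does not set uptake. It supports only that nothing ensures an even split. Gender, the example used for the 1:1 modifier, is itself among the priority patient characteristics.

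The protocol also does not promise 80% power under any particular imbalance. It says only that uncertainty led to the higher target.

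**Conclusion.** The point holds in conditional form. Read in the order written, the protocol's figures require 625 to 1000 included. The stated minimum of 800 supports 80% power only for scenarios needing up to 640 analysed, and about 71% for the scenario needing 800. In that top scenario at 20% loss, the target of 1000 gives 80.0% (79.6% at the planned 792) with 1:1 splits, and has nothing left for imbalance or higher loss. In lower scenarios, or with smaller loss, some reserve remains.

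The consequence is moderate. The target itself equals the correctly inflated number for the top scenario, so the fault lies in the stated minimum and in what the target is said to cover.

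The figures assume that 500 to 800 is the requirement before loss and that each value gives exactly 80% power at 1:1. They take the protocol's range as given. Whether that range follows from the stated interaction size is a separate question. The imbalance figures rest on assumed splits, independence of treatment and modifier, and a common standard deviation.

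**What to change.** In Sample size/power calculation:

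1. Restate the sentence on the minimum: up to 800 evaluable patients are needed, hence up to 1000 included at 20% loss. If 800 was instead derived from a 640-patient scenario, or already includes loss, say so and limit the 80% power claim to the scenarios it covers.
2. State that in the top scenario at 20% loss, 1000 does not also cover unequal surgery or modifier proportions or higher loss.
3. Report the detectable interaction at 792 analysed for a range of assumed surgical shares and modifier prevalences. For a difference of differences this is 2.802 × SD / √[792 × p(1−p)q(1−q)]. At 1:1 on both it is about 7.2 ODI points with SD 18 and 9.2 with SD 23.

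The cost is a rewording and a small table. No extra patients are needed. The downside is a less favourable power statement.

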### Feasibility of the study

The patient sample will be taken from orthopaedic spine units, rehabilitation centres, and pain clinics in CH and NZ. The feasibility of data collection in CH has been proved in prior joint ventures between the MEM Research Center and university and regional hospitals (e.g. Inselspital and Salem-Spital in Berne, Schulthess Clinic in Zurich, all of them offering surgical and conservative treatment, none of them working on a referral basis).

NZ has been chosen for comparison of differences across health care systems because of ideal starting conditions for this research project: NZ is a country with a traditionally high acceptance of clinical research. For example, the National Joint Register of patients who underwent total hip or knee replacement, established in 1999, has near 100% coverage.

The MEM Research Center in Berne coordinates the Swiss-based European Spine Registry of the Spine Society of Europe (SSE) [65-70]. In parallel to the planned bi-national multicentre study, a national spine registry for NZ could be implemented by the University of Otago. This National Spine Register – comparable to the existing National Joint Register – would address all patients with CLBP who report to a clinic in NZ, generating synergetic effects. All patients joining the National Spine Register could be asked to participate in the multicentre study as well, which would make data collection much easier.

Cooperation on successful doctoral studies in both countries already exists between the University of Berne and the University of Otago, NZ.

Furthermore, NZ has a manageable population size, which is comparable to CH. This setting and the observational nature of the study will ensure sufficiently high recruitment rates.

The respective acquisition of patient data will be coordinated at the MEM Research Center and the University of Otago. 2200 patients will be assessed for eligibility in CH and NZ combined (see figure 1). It can be assumed that 75% of these screened patients will be found eligible for enrolment. Out of these 1650 patients, presumably 990 (60%) will agree to participate in this study. Up to 20% of the patients can be expected to be lost to follow-up in the worst case scenario, so that, finally, 792 patients will be analysed according to the intention-to-treat principle. This estimate is based on data provided by a recent prospective cohort study comparing surgical and conservative treatment in a LBP population, with ODI as primary outcome measures [21].

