#### Conservative treatment and co-interventions

We defined the absence of a surgical treatment as conservative treatment. Different conservative treatments are considered as co-interventions. These co-interventions that also can be applied to the surgical patient group are biomedical, psychologically oriented (cognitive behavioural therapy), and socio-occupational interventions (return-to-work program). Biomedical interventions include physical treatments, exercise therapy, manual therapy, back schools, pharmacological procedures (analgetics, NSAID, opioids, antidepressants), and invasive nonsurgical treatments (acupuncture, injections, facet/nerve root blocks, neuroreflexotherapy, percutaneous electrical nerve stimulation, radiofrequency, intradiscal electrothermal therapy, intradiscal radiofrequency thermocoagulation, cryotherapy of the facets, alcohol denervation, temporary epidural catheters, permanent intrathecal pain-control pumps, and spinal cord stimulators).

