### Statistical Analysis

#### Outcomes

In this prospective cohort study, two interventions for CLBP are compared: surgical and conservative treatment. Subgroups of different surgical treatments can be distinguished. Nonsurgical co-interventions may have an effect on patient groups with surgical as well as with conservative treatment.

Follow-up data at six months will be analysed according to the intention-to-treat principle, except for those patients who change treatment groups before the beginning of the allocated treatment.

Changes in dependent outcome variables between baseline and follow-up at six months will be analysed by multiple linear regression models. Surgical and conservative treatment, patient characteristics, and co-interventions are independent variables. To address potential effect modification, we will then incorporate interactions between type of treatment and the different co-interventions and patient characteristics.

Highest priority among co-interventions will be given to the analysis of effects of cognitive behavioural therapy and return-to-work programs. Among patient characteristics highest priority in data analysis will be given to gender, age, and duration of work-absenteeism.

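### The set called intention-to-treat is the patients left after loss to follow-up, and tying a self-completed ODI to a clinic visit makes some of that loss avoidable

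*Protocol article*

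**What the plan says.** All references are to the Protocol article.

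- **Feasibility of the study** gives the patient flow. It starts from screening: "2200 patients will be assessed for eligibility in CH and NZ combined". Three quarters are taken to be eligible, and for consent it says "Out of these 1650 patients, presumably 990 (60%) will agree to participate in this study". Its allowance for loss is worded "Up to 20% of the patients can be expected to be lost to follow-up in the worst case scenario". From this it draws the number for analysis: "so that, finally, 792 patients will be analysed according to the intention-to-treat principle".
- **Sample size/power calculation** describes a loss of the same size as a missed appointment: "we assumed a 20% rate of patients who will not return on schedule to the six-month clinical visit". It adds that the main outcome is measured at that visit, and it responds to the loss by enlarging the sample.
- **Demographic and baseline characteristics** lists the ODI, SF-36, EQol-5D index and VAS under patient self-assessment. **Database** has research nurses hand out the questionnaires and collect them.
- **Statistical Analysis, Outcomes** applies intention-to-treat to the six-month follow-up data, "except for those patients who change treatment groups before the beginning of the allocated treatment". It models change from baseline by multiple linear regression.
- On group membership, **Inclusion and exclusion criteria** enrols patients just before they start surgery or further conservative care. **Conservative treatment and co-interventions** says "We defined the absence of a surgical treatment as conservative treatment", with no time point.

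**The concern.** Intention-to-treat normally promises two things: everyone who entered is in the analysis, and each stays in the group in which they started. The first promise is not kept by a set from which patients lost to follow-up have been subtracted. A reader of the eventual report would credit the result with a protection that it lacks.

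The risk is selection. Whether a patient comes back at six months may depend on how well they have done and on the kind of care they are in. If so, completers misstate the mean ODI change in each group, and if the misstatement differs between groups, the surgical-versus-conservative contrast is biased. Raising the target to 1000 restores precision but leaves this bias as it is.

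The second promise is unclear. A patient who starts conservative care and is operated on in month three is conservative if the group is the treatment begun. The same patient is surgical if absence of surgery is judged over the whole six months. The text does not say which reading applies.

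**Working it through.** **1. The plan's own figure.** Inputs from Feasibility of the study: 2200 screened, 75% eligible, 60% consenting, up to 20% lost.

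- 2200 × 0.75 = 1650
- 1650 × 0.60 = 990
- 990 × (1 − 0.20) = 792, which reproduces the stated figure exactly
- 990 − 792 = 198 participants outside the set in the worst case

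A set of all enrolled patients would be 990. Whatever the actual loss rate, the same subtraction is made and the remainder carries the label.

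**2. Size of a completer bias.** In one group, the bias in mean change is the share missing × the difference in mean ODI change between retained and missing patients. The documents give neither the gap nor the loss by group, so the following values are assumptions: loss of 25% and 15% (average 20%, the plan's figure) and non-returners improving 5 to 10 points less.

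| Assumed gap | Bias, group with 25% loss | Bias, group with 15% loss | Shift in contrast |
|---|---|---|---|
| 5 points | 0.25 × 5 = 1.25 | 0.15 × 5 = 0.75 | 0.50 |
| 10 points | 0.25 × 10 = 2.50 | 0.15 × 10 = 1.50 | 1.00 |

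With 20% loss in both groups and the same gap, each group mean is off by 0.20 × 5 = 1 to 0.20 × 10 = 2 points, and the contrast is off by zero. Against the 10-point difference that the sample size section calls clinically relevant, 0.5 to 1.0 point is 5% to 10%.

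**3. Precision.** Analysing 792 rather than 990 multiplies the standard error by √(990/792) = 1.118, so it is about 12% larger than with full retrieval. The sample size section already allows for this.

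**4. How many patients the group definition could touch.** The Background reports crossover within two years, in an earlier observational cohort, of 22% from conservative care to surgery and 4% among surgical patients. With 990 split 1:1 (495 per group, the split assumed in the sample size section):

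- 495 × 0.22 = 109 conservative patients
- 495 × 0.04 = 20 surgical patients

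Follow-up here is six months and no six-month rate is given, so these counts are only an upper guide.

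**The case against.** The strongest reply is that 792 appears in a feasibility projection, as a worst case, and does not define an analysis set. That stands: the documents do not say that 198 patients will be dropped, nor that a late questionnaire will be discarded. The label is still applied to the remainder after loss, so the wording point survives.

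Second, the handling of missing data may be set out in an analysis plan that is not shown, and linear regression is compatible with imputation. This also stands, so the absence of a missing-data method is not part of the point. What remains is what the article does state: the label, and the visit at which the outcome is captured. An article may also omit a postal fallback that exists in practice. If there is one, saying so settles that part. The exclusion of patients expected to be lost, or unwilling to complete questionnaires, should reduce the loss, but the plan still budgets up to 20%.

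Third, a reader might infer that defining conservative treatment as the absence of surgery contradicts intention-to-treat. The documents do not support that. The definition can be read as describing the option chosen at entry, which fits both the inclusion criteria and the statistical section. It conflicts only if read as treatment received over six months. Nor does this ambiguity make the analysis a completer analysis; only the loss does that. A reader might also infer that patients who switch before treatment begins are removed. The text only exempts them from the principle, and they may equally be analysed under the treatment they start.

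Fourth, one might scale the 0.5 to 1.0 point to the treatment-by-modifier interaction. If the loss differential and outcome gap are the same at both levels of a modifier, the bias in the interaction is zero. A non-zero figure would need a differential that itself varies by level. Expressing it as a share of the interaction sought would also need a main treatment effect, which the sample size section never states.

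**Conclusion.** The point holds in a limited form. The patients described as analysed by intention-to-treat are those remaining after loss to follow-up (792 of 990 in the worst case), which is a completer set. Some of the loss is avoidable, because a self-completed outcome is tied to an on-schedule clinic visit. The group definition is ambiguous across three sections and needs reconciling, but it is not a contradiction.

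Under the assumptions in the table, the treatment contrast moves by 0.5 to 1.0 ODI point. This rests on unequal loss and on non-returners doing worse, neither of which the documents establish. The documents also do not show which treatment would be favoured, either by loss or by later crossover. The point is worth acting on because the remedy is cheap and because a larger sample cannot remove the bias.

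**What to change.** 1. **Retrieve the outcome.** Collect the ODI, SF-36, EQol-5D and VAS by post or phone, within a stated window, from patients who miss the six-month visit. Record the mode of completion. The physician-rated outcomes would still need the visit.
2. **Label the sets correctly.** In Statistical Analysis (Outcomes) and Feasibility of the study, call the patients with follow-up a completer set. Keep intention-to-treat for all enrolled patients, grouped by treatment begun. Report a sensitivity analysis for those still missing, with assumptions that may differ by treatment group. Imputing the outcome from baseline data alone would add little to a regression that already adjusts for those variables, so retrieval matters more.
3. **Reconcile the grouping.** Align Inclusion and exclusion criteria, Conservative treatment and co-interventions, and Statistical Analysis (Outcomes) so that the analysis group is fixed at the treatment begun. Later surgery should not reclassify a patient, and patients who switch before treatment starts should be analysed under the treatment they begin.

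The cost is postage, some nurse time and a few sentences of text. The downside is mixed modes of questionnaire completion.
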